## Abstract

**Background:**

Childhood obesity accompanied by lower levels of health-related physical fitness (HRPF) is a major threat to public health both internationally and locally. Children with intellectual disability, especially adolescents, have a higher risk of being overweight/obese and having poor HRPF levels. Therefore, more interventions are needed to help this population attain their optimal health levels. However, there has been relatively limited research on this population compared with on their typically developing peers.

**Objective:**

The proposed study aims to fill this knowledge gap by developing and examining the success of a physical activity (PA) intervention for the target population.

**Methods:**

The proposed study will be a 12-week, school-based randomized controlled trial. The participants (N=48) will be recruited from special schools for students with mild intellectual disability and then randomly allocated to either the intervention group (IG) or the wait-list control group (CG). During the intervention period, the participants in the IG will receive a fun game–based moderate-to-vigorous PA (MVPA) training program (2 sessions/week, 60 minutes/session, for a total of 24 sessions). The intensity of the activities will increase in a progressive manner. Participants in the CG will receive no program during the study period, but the same PA program will be provided to them after the completion of the study. To observe and evaluate the sustaining effects of the intervention, follow-up testing will be scheduled for the participants 12 weeks after the intervention concludes. The study outcomes will include primary outcomes (obesity- and fitness-related outcomes) and a secondary outcome (blood pressure). All of the measurements will be taken at 3 time points. After the follow-up tests, the same PA training program will be provided to the participants in the CG.

**Results:**

This study is ongoing. The participants were recruited from October 2020 to November 2020. The total duration of the study is 13 months. Study results are expected at the end of 2021.

**Conclusions:**

The proposed study is expected to reduce obesity and improve HRPF levels in children with intellectual disability. If proven effective, the intervention will be made accessible to more special schools and mainstream schools with students with intellectual disability. Furthermore, the study can serve as an example for international researchers, policy makers, and members of the public who are seeking to tackle the problem of obesity and poor HRPF among children with intellectual disability.

**Trial Registration:**

ClinicalTrials.gov NCT04554355; https://www.clinicaltrials.gov/ct2/show/NCT04554355

**International Registered Report Identifier (IRRID):**

PRR1-10.2196/25838

## Introduction

Childhood obesity accompanied with lower levels of health-related physical fitness (HRPF) is a major threat to public health internationally and locally [1]. The global prevalence of overweight and obesity among children has risen dramatically from 4% in 1975 to over 18% in 2016 [2]. This rising trend has been recorded in a wide range of countries [3]. For example, in the United States, obesity prevalence increased from 13.5% in 1995 to 18.5% in 2016 [2]. In China, the prevalence of overweight and obesity increased from 1.1% in 1985 to 20.4% in 2014 [4]. In terms of HRPF levels, the most update-to-date data showed that only 42% to 46% of children had adequate cardiopulmonary fitness (CPF) [5]. Studies have also demonstrated a global decline in CPF levels of 0.36% per year [6]. There is clear evidence that childhood obesity accompanied with lower levels of HRPF leads to short- and long-term risks, including cardiovascular diseases, metabolic syndrome, osteoporosis, type 2 diabetes, hypertension, and certain types of cancer [7,8].

Children with intellectual disability, who account for approximately 1% of the entire pediatric population, are more vulnerable than their typically developing (TD) peers to obesity and lower levels of HRPF [9,10], as they tend to be less active and less empowered to choose and adopt healthy behaviors [3]. The global prevalence of overweight and obesity in children with intellectual disability is 30% to 33% [9], and the risk of developing overweight and obesity is 1.54 to 1.80 times higher in adolescent children with intellectual disability (aged 12 to 18 years) than in their TD peers [3]. In terms of HRPF levels, a cross-sectional study found that 71% to 91% of children with intellectual disability (aged 12 to 18 years) scored below the reference values (for TD children) in CPF and muscular fitness [11].

Therefore, given the high prevalence of obesity and poor HRPF levels, children with intellectual disability, especially adolescents, should be a target population for reducing obesity and improving HRPF levels. Compared with the large body of research on effective interventions for obesity and lower levels of HRPF among TD children, few efforts have been made to examine the effectiveness of interventions for children with intellectual disability. To date, 3 reviews have examined intervention effects on changes in body weight and/or HRPF levels [12-14] in this population. Harris et al [12] examined the effects of 6 physical activity (PA) interventions that were described as including aerobic and resistance activities. However, no significant effects were found on any obesity-related outcomes. The second review, by Maïano et al [13], focused on lifestyle interventions, including PA, diet, health education, and cognitive behavioral strategies. The review of 9 studies concluded that interventions involving PA were effective in reducing body weight, BMI, fat mass, and peak oxygen consumption per unit time/peak power, and increasing peak power, maximal upper and lower limb strength, and number of sit-ups. However, inconsistent results were found for body fat percentage, waist circumference, and peak heart rate [13]. A third review [14] examined the effects of 6 interventions for excessive weight among children with intellectual disability. The intervention approaches included PA and parental engagement. However, no consistent results were found for any of the intervention types.

Based on the 3 reviews, we cannot draw any firm conclusions on intervention effects because of the limited number of studies involved. In addition, the most recent of the 3 reviews was published in 2014. Since 2014, there has been an increase in the number of interventions in the target population. Therefore, an updated review on the topic is needed to identify effective interventions for this population.

Hence, given the above evidence, we conducted a systematic review and meta-analysis on this topic (data have not yet been published). Our findings suggested the following: (1) PA was the predominant component to be adopted into interventions, with 27 of the 29 identified interventions implementing PA; (2) PA contributes to improving CPF (50.50 m, 95% CI 22.23-78.77; *P*<.001), lower limb muscular strength (19.41 kg, 95% CI 11.32-27.49; *P*<.001), and upper limb muscular strength (4.42 kg, 95% CI 0.12-8.73; *P*=0.04) in children with intellectual disability; and (3) the limited research related to this population prevented us from drawing any confirmed conclusions on relationships with obesity.

In relation to the above, we would like to develop a PA intervention to reduce obesity and improve HRPF levels in adolescents with intellectual disability. The proposed study will be a 12-week, school-based PA program with a 2-armed randomized controlled trial (RCT) design. The primary outcomes will be obesity- and HRPF-related outcomes. Blood pressure will be evaluated as a secondary outcome, as some common noncommunicable diseases, such as hypertension and diabetes, that occur in adulthood have become more prevalent in children, mainly due to unhealthy lifestyles and obesity [15]. The objectives of the proposed study are to evaluate the effectiveness of the intervention on obesity- and HRPF-related outcomes (primary outcomes) and blood pressure (secondary outcome) and to evaluate sustainable effects of the intervention on all outcomes, with a comparison with a control group (CG) and adjusted for confounding factors (eg, sociodemographic and lifestyle factors).

## Methods

### Study Design

The proposed study will be a 12-week, school-based RCT (Figure 1) that will take place in the Chinese mainland. The participants will be recruited from special schools for students with mild intellectual disability and then randomly allocated to either the intervention group (IG) or the wait-list CG. During the 12 consecutive weeks of the study, the participants in the IG will receive a fun game–based moderate-to-vigorous PA (MVPA) training program (2 sessions/week, 60 minutes/session, for a total of 24 sessions). The intensity of the activities will increase in a progressive manner. Those in the CG will receive no intervention. All of the participants (in both groups) will be asked to maintain their regular activities during the intervention period. To observe and evaluate the sustaining effects of the intervention, follow-up testing will be scheduled for all of the participants 12 weeks after the intervention ends. The follow-up period of 12 weeks has been chosen to fit the regular school calendar of the local special schools. The study outcomes will include primary outcomes (obesity- and fitness-related outcomes) and a secondary outcome (blood pressure). In addition, control variables including sociodemographic factors, subjective PA levels, screen time, eating habits, and sleep duration will be collected using a questionnaire. All of the measurements will be taken at 3 time points: Test 1 (T1, before the intervention), Test 2 (T2, immediately following the intervention), and Test 3 (T3, after the 12-week follow-up period). After the follow-up tests, the same PA training program will be provided to the participants in the CG.

**Figure 1 figure1:**
[figure not shown]
Flow diagram of the study. *Measurements at Tests 1, 2, and 3 will include obesity- and fitness-related outcomes (primary outcomes), blood pressure (secondary outcome), and confounding variables (including demographic information, subjective physical activity [PA] levels, screen time, sleep duration, and eating habits).

### Study Population

#### Target Population and Selection Criteria

The target population of the study will be overweight and obese students aged 12 to 18 years in special schools for those with mild intellectual disability. Overweight and obesity will be defined according to commonly used age- and gender-specific BMI cutoff points (Multimedia Appendix 1) [16]. Participants will be selected according to the following inclusion criteria: (1) children with mild intellectual disability; (2) aged 12 to 18 years; (3) overweight or obese; and (4) at least one family member who is able to attend the program with the participant. The exclusion criteria will be children (1) with a physical disability; (2) with a medical predisposition toward obesity (such as genetic syndrome) that could interfere with the results of the study; (3) with contraindications for PA (eg, severe heart disease); or (4) who participated in other obesity- or fitness-related programs in the past 6 months. This research proposal has been reviewed and approved by the Research Ethics Committee of Hong Kong Baptist University.

#### Sample Size Estimation

The sample size will be calculated using G*Power software (version 3.1.9.4). Previous research has shown that a medium effect size of 0.21 is appropriate [17]. Setting a significance level of *P*<.05, a power level of 80%, and a constant correlation of 0.5, and assuming a 20% dropout rate, a total sample size of 48 participants (24 participants in each group) will be needed.

#### Participant Recruitment

Invitation letters will be sent to special schools in China. If a school agrees to participate, the physical education (PE) teachers at that school will be contacted to help with the initial recruitment of participants by sending a screening questionnaire to their students to determine if they meet the eligibility criteria for study participation. A written informed consent form will be attached to the screening questionnaire to obtain parental consent in advance. Next, the heights and weights of all eligible participants will be objectively measured at their home school. A BMI will be calculated for each student, and students of normal weight will be removed from the list of potential participants. The recruitment will continue until the estimated sample size (n=48) is reached.

#### Randomization and Blindness

We will randomly and equally assign the 48 participants to the IG and CG using block randomization [18]. The random allocation sequence will be computer-generated by a blinded statistician outside of the research term. Masking of participants will be achieved by the wait-list design, where participants assigned to the CG will receive the intervention after the study and therefore will not know that they are in the CG. Furthermore, outcome assessors and statistical analysts will also be masked to the group allocation of the participants.

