#### Strategies to Increase Participation and Decrease Dropouts

Previous intervention studies have indicated that parents might refuse to participate if their children do not receive the interventions and thus do not reap the potential benefits of the interventions. To address this issue, we will adopt the wait-list CG design to ensure that all participants will have an equal chance to undertake the PA training program. The PA training program will be free to the participants, and a 100 Chinese Yuan (US $15.45) coupon will be rewarded to the parent of each participant, which will help to increase participation. In addition, the potential health benefits of the project, such as helping participants decrease body weight and improve HRPF levels, will be clearly described to the participants and their parents to increase their interest in participating.

To reduce dropout rates, rewards (eg, stickers) will be given to participants who complete each intervention session. Stationery (eg, pens, erasers) will be given as a reward to participants who achieve an attendance rate of 85% or higher. In addition, only participants who complete the entire study will receive the 100 Chinese Yuan reward, which will also help to reduce withdrawals.

Establishing effective communication channels with parents will increase their confidence in the project. The participants’ health status (eg, weight change) and session performance will be reported to their parents by messages upon request. In addition, the participating schools will serve as a communication bridge between the research team and participants/parents. Maintaining strong communication with the schools’ PE teachers and nurses will also help the research team to understand the health needs of the participants/parents, which may help to decrease dropout rates.

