##### Safety Assurance

In each training session, the ratio of tutor to participant will be 1:3. Hence, there will be enough tutors to ensure the participants’ safety. The tutors will pay close attention to participants’ exercise performance to prevent sports injuries. In addition, all of the games are from the game series promoted by the Hong Kong Physical Fitness Association. They are recognized as safer than most self-designed games. As different exercise units may have different characteristics, the safety procedures will vary according to the exercises (see Multimedia Appendices 2 to 7). Furthermore, the equipment used in the program will not have sharp edges. It is better to choose equipment that the participants are familiar with or often used in their PE classes. Moreover, drinking times will be arranged in each training session (eg, participants will drink water every 20 minutes). Finally, in case of emergency, at least one PE teacher from each participant school will be required to attend and assist with each exercise session and on-site data collection.

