##### PA Instructor Recruitment and Training

The tutors should have some knowledge of PE and have experience leading PE courses for students with special needs. Three training sessions (60 minutes per session) will be provided to all tutors. During the sessions, we will explain the background, objectives, and significance of the study and the characteristics of the participants. Then, we will introduce the interventions and the methods for exercise intensity control and safety for each exercise unit. Finally, all of the study measurements will be introduced.

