### Description of Control

Initially, no intervention will be delivered to the participants in the CG during the intervention period. Also, they will not be permitted to join any other related programs. They will be asked to continue their usual school activities. All participants in the CG are expected to receive the same PA program after the completion of this study to ensure that they have the same opportunity to improve their health.

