### Quality Control

Manual and operational procedures will be prepared for all of the team members. Three training sessions (60 minutes/session) will be provided. Monthly and ad hoc research meetings with experts (university teachers) in the PA area, student helpers, and PE teachers/nurses in the special schools will be held to ensure the success of the proposed study. To promote a uniformly high performance, we will conduct unannounced quality assurance inspections (2 times/month) in the field. The data will be checked by auditors immediately and entered twice to enhance accuracy. Moreover, on the written informed consent form, we will request that the participants in the IG and their parents do not communicate with any parents and classmates in the school about the intervention to avoid contamination and behavioral spillover. In addition, we will seek the participating schools’ help to remind them and monitor and prevent occurrences of such behavior.

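### Participant masking is claimed from a wait-list design that cannot provide it, and assessor masking is put at risk by PE teachers who attend the sessions and also assist with testing

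*Protocol article*

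**What the plan says.** Randomization and Blindness makes two masking claims. The first concerns participants and rests on the wait list: "participants assigned to the CG will receive the intervention after the study and therefore will not know that they are in the CG". The second is that "outcome assessors and statistical analysts will also be masked to the group allocation of the participants". No mechanism is given for the second.

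Other sections describe what each group experiences and who is present:

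- **Control condition.** Description of Control states that "no intervention will be delivered to the participants in the CG during the intervention period". No sham or attention control is described.
- **Intervention.** Study Design gives two 60-minute sessions a week for 12 weeks. Training Time Arrangement places them in school hours, outside PE class.
- **Rewards and feedback.** Strategies to Increase Participation and Decrease Dropouts gives stickers for completed sessions and stationery for attendance of 85% or more. It adds that "session performance will be reported to their parents by messages upon request".
- **Staff.** Safety Assurance says that "at least one PE teacher from each participant school will be required to attend and assist with each exercise session and on-site data collection". The tutor training described in PA Instructor Recruitment and Training ends with: "Finally, all of the study measurements will be introduced".
- **Walk test.** A trained examiner measures and records the distance. Each child has a university student helper who gives direction and encouragement.

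**The concern.** A wait list settles when controls are treated. It does not conceal who is being treated now. The protocol presents it as a masking device, so a report that follows the protocol would describe participants as masked when they are not.

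For assessors, the protocol claims masking in one section and in another gives a part in data collection to people who necessarily know which children trained. If they do more than stand by, the claim fails for the outcomes they touch.

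The stake is the fitness half of the primary outcomes. A child who knows that he or she has trained, or a helper who knows it, may try harder or encourage more at the tests after baseline. The resulting difference would look like a treatment effect. Families have also been told beforehand to expect better fitness (Strategies to Increase Participation and Decrease Dropouts). The limitations in the Discussion cover self-reported activity, severity of disability and school type, but not masking.

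**Working it through.** The masking claims contain no figure to reproduce, so the check sets the sections side by side.

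**1. Participants.** Exposure in the intervention group is 2 sessions × 12 weeks = 24 sessions; in the control group it is 0. The sessions are visible, supervised and rewarded. Controls are offered the programme only after the 12-week follow-up tests, so the difference in experience is in place at both T2 and T3. The reason given in Randomization and Blindness concerns what happens after T3 and cannot affect what families know at T2 or T3.

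The same article adopts the wait list because parents might refuse if their children receive no programme. It can reassure parents only if they are told about it.

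**2. Assessors.**

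| Section | Content | Bearing on masking |
|---|---|---|
| Randomization and Blindness | Assessors masked | The claim |
| Safety Assurance | The PE teacher role covers every session and data collection | Conflicts, if assisting includes any part of testing |
| 6-Minute Walk Test | Examiner records; student helper encourages | Neither is described as a PE teacher or tutor; masking not stated |
| PA Instructor Recruitment and Training | Measurements introduced to tutors | Does not say that tutors test |

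The sections leave room for a masked examiner, but they do not secure one.

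**3. Outcomes exposed.** There are six obesity-related primary outcomes: weight, BMI, waist, hip, waist-to-height ratio and body fat percentage. There are five fitness-related ones: 6-minute walk, sit-to-stand, sit-ups, handgrip and sit-and-reach. The total is 6 + 5 = 11. The first four fitness tests ask for maximal performance, and sit-and-reach depends on cooperation. The obesity measures come from a device or tape, or are computed from such readings, and are less exposed.

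**4. Illustration with assumed bias.** The document gives no size for the bias, so the shifts below are assumptions.

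Group sizes: reading the stated 0.21 as Cohen's f for the group-by-time interaction (2 groups, 3 time points, correlation 0.5, alpha 0.05, sphericity assumed), λ = 0.21² × 38 × 3 / (1 − 0.5) = 10.05 with 2 and 72 degrees of freedom. This gives power 0.800 at N = 38. Then 38 / 0.8 = 47.5, rounded up to 48, which reproduces the planned total. So n per arm is 19 evaluable, or 24 with no dropout.

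Suppose there is no true effect and a spurious between-arm shift of b standard deviations in the change score. With SE = √(2/n), which is 0.324 for n = 19 and 0.289 for n = 24, the two-sided false-positive rate per outcome is approximately Φ(b/SE − 1.96) + Φ(−b/SE − 1.96).

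| Assumed b | 19 per arm | 24 per arm |
|---|---|---|
| 0.1 | 6.1% | 6.4% |
| 0.2 | 9.5% | 10.7% |
| 0.3 | 15.2% | 18.0% |
| 0.5 | 33.8% | 41.0% |

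The rate rises with n, so a larger sample does not cure this error.

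**The case against.** The strongest case on the other side has five parts.

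- **Masking of participants is rarely possible against no intervention.** True, and the lack of masking is not itself a fault. The fault is to claim it. One might add that control families could think of themselves simply as a later intake. Even so, intervention families know that they have trained, so expectations still differ between arms.
- **The PE teacher sentence is about safety.** It closes the Safety Assurance section and is introduced as provision for emergencies. A trained examiner records the walk. This stands. A reader might infer that assessor masking is defeated, but the text does not show that PE teachers score anything, only that they assist.
- **Tutors and walk-test partners.** A reader might infer that tutors test, or that partners know the allocation. Neither is stated. Tutors are only introduced to the measurements.
- **The consent form.** A reader might infer that it discloses the arm, because "we will request that the participants in the IG and their parents do not communicate with any parents and classmates in the school". Participant Recruitment sends the form out with the screening questionnaire, before eligibility is settled. Data Collection Procedure mentions forms sent again after recruitment, without saying whether allocation is then known. The clause presumes that intervention families will come to know their arm, but it does not show that the form tells them. The point does not rest on it.
- **Direction of bias.** Both arms have an encouraging partner and hear of the same benefits, and contamination would dilute the contrast. So a bias towards the intervention group is likely, not proven. The questionnaires supply covariates, not outcomes, and add nothing to its size.

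The non sequitur about participants survives all of this, as does the unreconciled conflict over the PE teachers.

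**Conclusion.** The participant-masking claim is wrong as written. With no sham, and 24 school sessions against none, participants and parents will know who is being trained, whatever is offered later. Assessor masking is claimed without a mechanism and is put at risk by the dual role of the PE teachers; the document does not show that it fails. Analyst masking is not contradicted.

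Five of 11 primary outcomes are open to expectation bias. The false-positive rates shown depend wholly on the assumed shifts and on a normal approximation; they illustrate the mechanism and do not estimate this trial's bias.

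A reader might conclude that the whole trial is open-label. The documents do not support that: with roles separated, it would have masked assessors and analysts and unmasked participants.

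**What to change.** - **Randomization and Blindness:** delete the participant-masking claim. State that participants, parents, tutors and the PE teachers who attend sessions know the allocation, and that only outcome assessors and analysts are masked.
- **Safety Assurance:** limit PE teachers at testing to safety and emergency cover, with no instructing, encouraging, counting or recording.
- **6-Minute Walk Test:** require examiners and partners to be planned staff who delivered no training sessions and are not told the allocation.
- **Discussion, limitations:** list unmasked participants as a limitation on the fitness outcomes.

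The cost is wording, some reassignment of roles among existing staff, and a less favourable masking statement. Sample size, outcomes and analysis do not change. Expectation bias among the participants themselves remains and can only be acknowledged.
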